**Primary Immunogenicity readouts:**

1. Etoricoxib effect of TB specific immune responses: T cell proliferation and cytokine responses (change between day 0 and 140).
2. H56:IC31 vaccine immunogenicity: T cell proliferation and cellular cytokine responses 14 days post-immunization (day 98 and day 154).

3. Etoricoxib effect of H56:IC31 vaccine immunogenicity: T cell proliferation and cellular cytokine responses 14 days post-immunization (day 98 and day 154).

**Readouts:** 1. WB/PBMC ICS (cytokines responses). 2. T cell proliferation (cfse), 3. Tregs/maturity (CD25, FoxP3, COX-2). 4. Soluble biomarkers. 5. Monocyte responses (COX-2). 6. RNA analysis.

**Statistical Methods:** Non-parametrical methods to describe patient groups including matched pair statistics to determine primary endpoints within the four study arms.

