### **1.3.3 COX-2i improves TB specific immune responses and regulation *in vitro***

Functional studies on the effect of COX-2i upon immune cells, longitudinally collected from clinically characterized TB patients during therapy at our hospital and from our national partners, are currently in progress in our lab. We have previously described elevated levels of Treg subsets in active and latent TB (10). In studies of active TB patients during anti-TB chemotherapy we demonstrate a decrease in the fraction of *Mtb*-specific IFN- $\gamma$ -producing T cells stimulated by TB-specific antigens (ESAT-6, CFP-10) *in vitro* already after 2 weeks of efficient treatment, whereas the pool of IL-2+ cells increased over time (30). The Treg was still able to expand after *Mtb*-specific *in vitro* stimulation, but a decline in activated Treg was seen when COX-i was added to the cells. These pilot findings indicate that COX-2i could possibly block regulatory T cells and improve TB specific immunity. In the current study these data will form the basis for additional in-depth exploratory analysis of Tregs in TB infection.

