#### 7.1.3 Primary immunogenicity Endpoints

1. Etoricoxib effect of TB specific immunogenicity: T cell proliferation and cytokine responses (change between day 0 and 140)

2. H56:IC31 vaccine immunogenicity: T cell proliferation and cytokine responses 14 days post-immunization (day 98 and day 154 compared to day 84)
3. Etoricoxib effect of H56:IC31 vaccine immunogenicity: T cell proliferation and cytokine responses 14 days post-immunization compared to H56:IC31 alone.

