## **10.4 Statistical Analysis**

Groups will be compared with non-parametrical statistical methods throughout with two-ways tests using p-values equal to or below 0.05 as significant. No adjustments due to multiple comparisons will be performed.

Deviation from the original statistical plan will be described and justified in the Clinical Study Report. The investigators can make the decision regarding individual values belonging to a subject to be excluded from the statistical evaluations, but only when a protocol violation is considered to weaken any of the scientific aspects of the study. Missing data will not be substituted by estimated values, but will be treated as missing data by the method used.

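### The protocol gives conflicting analyses for the immune endpoints, and the within-arm version could not separate etoricoxib from the chemotherapy that starts on the same day

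*Protocol*

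**What the plan says.** The protocol gives four accounts of how the immune read-outs are analysed.

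- **Within arms.** The synopsis offers non-parametric methods for describing the groups of patients, among them "matched pair statistics to determine primary endpoints within the four study arms". Section 7.1.3 gives the etoricoxib effect as "T cell proliferation and cytokine responses (change between day 0 and 140" and vaccine immunogenicity as "day 98 and day 154 compared to day 84"; neither item names a comparator arm. Item 3 does: "T cell proliferation and cytokine responses 14 days post-immunization compared to H56:IC31 alone". The list of aims under the arm table in section 3 ties the etoricoxib effect to arm 1 and vaccine immunogenicity to arm 2.
- **Between groups, tested.** Section 10.4: "Groups will be compared with non-parametrical statistical methods throughout", two-sided, with p≤0.05 counted as significant.
- **Descriptive.** Section 10.4.6.1 has the primary evaluation rest on summaries, without formal tests.
- **Between groups, estimated.** Supplementary Tables 3 to 5 set the contrasts as arms 1+4 against 2+3 (day 0 to 84), arm 2 against 3, and arm 4 against 2 (both day 84 to 154). The supplementary statistical methods describe median regression of the change on treatment, with bootstrap confidence intervals.

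Section 10.4.6 limits all immunogenicity analyses to patients who took etoricoxib up to the sample in question and/or had one or more vaccine doses. Arm 3 receives neither, yet section 3 lists it as the control for immunogenicity.

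On the natural course, section 1.3.3 reports that during anti-TB chemotherapy the share of Mtb-specific IFN-gamma T cells fell "already after 2 weeks of efficient treatment, whereas the pool of IL-2+ cells increased over time". The synopsis has etoricoxib start together with chemotherapy on day 0.

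**The concern.** A paired within-arm comparison answers whether the read-out changed, not whether the study product changed it. Every patient receives chemotherapy throughout the window. For arm 1 the two treatments start on the same day, so a day 0 to 140 change contains both effects and nothing inside that arm can divide them. The investigators' own earlier data indicate that the chemotherapy part is not zero for IFN-gamma and IL-2, the cytokines measured by the ICS and ELISPOT assays.

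The protocol includes a chemotherapy-only arm that would remove this problem. But its text does not settle whether that arm enters the analysis of items 1 and 2, or whether those items are tested, estimated or only described. An analyst could follow the synopsis, section 10.4 or section 10.4.6.1 and claim to be following the protocol each time.

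**Working it through.** **Nothing to reproduce.** Section 10.1 states that no sample size calculation was made, and section 1.3.3 gives no size for the chemotherapy change. The figures below illustrate; they do not estimate.

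**Simulation.** 10,000 trials; 10 patients per arm, as planned; normally distributed within-patient changes with SD 1; the same chemotherapy shift in the active and control arms; no drug effect; two-sided 0.05. The within-arm test is the exact Wilcoxon signed-rank test in the active arm. The between-arm test is the exact Mann-Whitney test on the changes, active against control. Monte Carlo standard error is at most √(0.25/10,000) = 0.5 percentage points.

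| Assumed shift (SD of the change) | Significant within arm | Significant against controls |
|---|---|---|
| 0 | 4.6% | 4.4% |
| 0.25 | 10.7% | 4.5% |
| 0.5 | 27.9% | 4.2% |
| 0.8 | 59.0% | 4.4% |
| 1.0 | 78.3% | 4.2% |

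The within-arm rate depends entirely on the assumed shift. The comparison with controls is unaffected, because the shift is common to both arms and cancels.

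**How far section 1.3.3 reaches.** It covers IFN-gamma and IL-2 responses to ESAT-6 and CFP-10. It says nothing on T cell proliferation or on whole H56. It does not isolate change after day 84, where the vaccine window opens. The direction also matters: rising IL-2 could mimic a vaccine response, while falling IFN-gamma would hide one.

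**What the between-arm contrast can detect.** By normal approximation with equal SDs, 80% power at two-sided 0.05 needs a difference of (1.960 + 0.842) × √(1/n₁ + 1/n₂) SD.

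- 10 against 10: 2.802 × √0.2 = 1.25 SD.
- 20 against 20 (arms 1+4 against 2+3): 2.802 × √0.1 = 0.89 SD.

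Enrolment runs in two parts: arms 1, 2 and five controls (10, 10, 5), then arm 4 and five controls (10, 5). Keeping to patients randomised together:

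- Arm 2 against its concurrent controls, 10 against 5: 2.802 × √0.3 = 1.53 SD.
- Etoricoxib to day 84, stratified by part. Part A is 10 against 15, information 1/(1/10 + 1/15) = 6.00. Part B is 10 against 5, information 1/(1/10 + 1/5) = 3.33. The sum is 9.33, giving 2.802/√9.33 = 0.92 SD.

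**The case against.** The strongest reply is that one synopsis line should not outweigh the rest of the protocol. Section 10.4 is the statistical section and compares groups. Section 10.4.6.1 plans no formal tests of these endpoints, so a count of significant paired tests describes an analysis it does not intend. Section 7.1.3 lists outcome variables, and a change from day 0 is a legitimate outcome for a between-group analysis. The synopsis sentence mentions description and does not mention testing; it could mean only that each patient's own change is computed. The supplement shows between-group contrasts for all three hypotheses and refers to a final SAP that is not at hand. Immune effects are also a secondary objective in an exploratory phase I trial.

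Most of this stands, and it limits the consequence. A reader might infer that the trial would credit chemotherapy effects to etoricoxib or the vaccine. The documents do not support that, because it follows only if the within-arm version prevails. A reader might also infer that the controls would have no role; section 3 and the supplement's contrasts say otherwise. That arm 3 would show the same change as arm 2 after day 84 is not established anywhere.

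The reply does not remove the contradiction. The sections differ, and no rule ranks them. Section 7.1.3 names a comparator for item 3 and not for items 1 and 2. The supplement is written in the past tense and uses day 0 to 84 rather than day 0 to 140, so it shows a workable analysis without correcting the protocol text.

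**Conclusion.** The protocol contradicts itself on whether the immune endpoints are within-arm, between-arm or descriptive, and section 10.4.6 taken literally drops the control arm. One of the stated versions, the within-arm one, cannot separate etoricoxib from chemotherapy in arm 1. This is firm for the logic of item 1, and supported by the protocol's own data for the IFN-gamma and IL-2 read-outs only. For the vaccine window a bias in either direction is possible, but the document does not show one.

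The size is unknown. False-positive rates from about 5% to 78% come from assumed shifts of 0 to 1.0 SD, normal changes and 10 patients; at a small shift of 0.25 SD the rate is about 11%. They count significant changes in the direction of the assumed shift, and not every such change would be read as benefit. The correction is worth making because it is specific and cheap, not because a wrong result is shown to follow.

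**What to change.** 1. Reword the synopsis sentence and section 7.1.3 items 1 and 2 so that the estimate is the between-arm difference in change with a 95% confidence interval: etoricoxib against no etoricoxib for item 1, arm 2 against arm 3 for item 2.
2. Respect the two enrolment parts, by stratifying on part or using concurrently randomised controls.
3. State one window for item 1. To day 84 no arm has had the vaccine, so arms 1+4 can be set against 2+3. To day 140 that pooling would assume that etoricoxib does not alter the vaccine response, which is what item 3 asks; arm 1 against arm 3 avoids the assumption.
4. State in section 10.4.6 that arm 3 is analysed.
5. Align sections 10.4 and 10.4.6.1 on whether p-values are reported for these endpoints and what status they have.
6. Keep paired within-arm changes as description, without p-values.

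This needs wording in a few places and no new data. The price is precision: intervals widen and fewer results will be nominally significant. Stratifying the etoricoxib contrast costs little (0.92 against 0.89 SD detectable with 80% power). Restricting the vaccine contrast to concurrent controls costs more (1.53 against 1.25 SD), which is a reason to report estimates with intervals.

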## LIST OF ABBREVIATIONS

|               |   |                                                             |
|---------------|---|-------------------------------------------------------------|
| AE     | - | adverse event                                 |
| AFS    | - | acid fast staining                            |
| ALAT   | - | alanine aminotransferase                      |
| ASA    | - | acetyl salicylic acid                         |
| ASAT   | - | aspartate aminotransferase                    |
| ART    | - | antiretroviral therapy                        |
| cAMP   | - | cyclic adenosine mono phosphate               |
| CFR    | - | code of federal regulations (USA)             |
| CHD    | - | coronary heart disease                        |
| COX    | - | cyclooxygenase                                |
| COX-2i | - | cyclooxygenase-2 inhibitors                   |
| CK     | - | creatine kinase                               |
| CRF    | - | case record form                              |
| CRO    | - | contract research organization                |
| CRP    | - | C-reactive protein                            |
| CSA    | - | Clinical Study Agreement                      |
| CTC    | - | Common Toxicity Criteria                      |
| CTCAE  | - | Common Terminology Criteria for Adverse Event |
| DAE    | - | Discontinuation due to Adverse Event          |
| DMARDS | - | disease-modifying anti-rheumatic drugs        |
| DOT    | - | directly observed therapy                     |
| EC     | - | ethics committee                              |
| ESR    | - | Erythrocyte Sedimentation Rate                |
| GCP    | - | good clinical practice                        |
| HIV    | - | human immunodeficiency virus                  |
| hGC    | - | human chorionic gonadotropin i serum          |
| IB     | - | Investigator's Brochure                       |
| ICF    | - | Informed Consent Form                         |
| ICH    | - | international conference on harmonization     |
| ICS    | - | intracellular cytokine staining               |
| IFN    | - | interferon-gamma                              |
| IMP    | - | Investigational Medicinal Product             |
| LTBI   | - | latent TB infection                           |
| LDH    | - | lactate dehydrogenase                         |
| MDR-TB | - | multi-drug resistant TB                       |
| Mtb    | - | mycobacterium tuberculosis                    |
| NSAID  | - | non-steroid anti-inflammatory drug            |
| NYHA   | - | New York Heart Association                    |
| PBMC   | - | peripheral blood mononuclear cells            |
| PCI    | - | percutan coronar intervention                 |
| PGE    | - | prostaglandin E                               |
| PKA    | - | protein kinase A                              |
| SAE    | - | serious adverse event                         |
| SOP    | - | standard operating procedure                  |
| SPC    | - | summary of product characteristics            |
| SUSAR  | - | Suspected Unexpected Serious Adverse Reaction |
| TNF    | - | tumor necrosis factor                         |
| TB     | - | tuberculosis                                  |
| XDR-TB | - | extensively drug-resistant TB                 |

# 1 INTRODUCTION

## 1.1 Background

### 1.1.1 The TB epidemic

The World Health Organization estimates that there were 9.0 million incident active tuberculosis (TB) cases and 1.5 million deaths caused by TB in 2013 (1). A fifth of previously treated TB cases with recurrent TB disease have multi-drug resistant (MDR)-TB and extensively drug-resistant TB (XDR-TB) has been reported by 84 countries. MDR-TB may take years to treat with expensive and toxic second-line drugs with uncertain efficacy. Further, the shifting of the TB epidemic towards XDR-TB with very restricted treatment options could reverse many of the major gains made in TB control and increase spread, morbidity and mortality. This calls for new treatment modalities that could be affordable and simple alternative for a substantial number of patients with MDR-TB and XDR-TB in resource-poor countries.

### 1.1.2 Immune pathogenesis and regulation in TB

*M. tuberculosis* (*Mtb*) normally enters the host through mucosal infection and targeting of the bacteria to professional phagocytic cells induces rapid innate inflammatory responses with subsequent production of cytokines and chemokines and formation of the primary granuloma surrounded by activated monocytes, macrophages and lymphocytes (2). In the majority of cases, TB infection is successfully contained, but persists as latent infection, whereas some succumb to reactivation and develop active TB, typically seen in immune suppressed patients. CD4 T cells are induced early in infection, whereas CD8 T cells, also recruited to the lung and granulomas during TB infection, expand in the late stages (3). Host control of TB is dependent on the T helper (Th) 1 cytokines interferon-gamma (IFN- $\gamma$ ) and tumour necrosis factor- $\alpha$  (TNF- $\alpha$ ) as well as proper activation of macrophages, since hyper-activated macrophages are typically found in progressing TB lesions (4). The role of TNF- $\alpha$  is illustrated by the rapid reactivation of latent TB in humans treated with TNF- $\alpha$  receptor antagonists (5) and the association of TNF- $\alpha$  production with protection in animal models (6). Polyfunctional T cell responses (IFN- $\gamma$ +IL-2+TNF- $\alpha$ +) have potential to serve as correlate for protective immunity since they seem to dominate in contained TB (7,8), but the T cell characteristics required for protection and optimal correlates for TB vaccine immunogenicity are yet to be established (9). T regulatory cells (Treg), a subset of CD4 T cells with immune regulatory properties that suppress Th1 cells and IFN- $\gamma$  production are expanded in active TB (10,11) and may suppress proper vaccine responses. Thus, the overall contribution to TB immunity by all these immune cell subsets has implications for both the design and strategy of post exposure vaccines and proper correlates of protection and needs to be further studied.

### 1.1.3 The cyclooxygenase-prostaglandin E2 pathway in TB

Prostaglandin E2 (PGE2) is produced by cyclooxygenase-2 (COX-2) in inflamed tissue and deregulates the protective immune response against TB and suppresses T cell mediated immunity (12). Co-investigator [name] and colleagues have established the role of cyclic adenosine monophosphate (cAMP) and protein kinase A (PKA) – Csk – Lck inhibitory pathway as a general mechanism in chronic inflammation that inhibits T cell signaling and activation through antigen receptors on lymphoid cells (13,14). Peripherally induced Tregs express COX-2, secrete PGE2 and thus enhance cAMP levels within effector cells so this mechanism may also be involved in the inhibitory function of Tregs (15). Similarly, monocytes and macrophages stimulated with a number of bacterial inflammatory mediators potently induce T cell cAMP levels and T cell dysfunction (16). Reduction of cAMP levels in T cells by reducing production of PGE2 via COX-2 inhibitors (COX-2i) and thereby EP receptor stimuli to T cells can therefore reverse this process and restore T cell responsiveness to vaccine antigens as we have shown for HIV-infected patients (17-19). Our hypothesis is that inefficacy of cellular immunity in TB lesions is closely linked to the chronic inflammation and resulting cAMP-mediated activation defects in the T cells. Since human active TB infection is dominated by macrophage activation in granulomatous inflammation, it is relevant to study whether hyperexpressed PGE2 and COX-2 contribute to T cell dysfunction and the effect of COX-2i in active human TB.

## 1.2 Pre-Clinical & Clinical Experience with COX-2i and H56:IC31

### 1.2.1 Pre-clinical studies of COX-2i in experimental animal TB models

Animal models support PGE2 as a significant factor in the pathogenesis of a dysfunctional hyper-activated immune system in TB. Studies of experimental pulmonary TB in BALB/c mice have shown that during early infection bacilli are efficiently phagocytised by lung macrophages that secrete pro-inflammatory cytokines (TNF- $\alpha$ , IL-1) and accordingly present bacillary antigens to IL-12 and IFN- $\gamma$  producing Th1 cells (12). During progressive disease Th2 cells emerge and an overproduction of anti-inflammatory and immunosuppressive molecules such as cortisol, PGE2, and transforming growth factor-beta (TGF- $\beta$ ) takes place that next downregulate cell-mediated immunity, enabling bacilli growth and progressive tissue damage. When PGE2 production was suppressed by COX-2i in animals with advanced disease, reductions in pulmonary inflammation and bacillary load took place in parallel with reversal to a Th1 cell profile (12,20). Further, the COX-2i celecoxib improved the 60-day survival of *Mtb*-infected mice to 100% with reduced lung levels of PGE2, bacillary load and inhibitory IL-10, whereas proinflammatory IL-12, IFN- $\gamma$  and alveolar macrophage nitric oxide synthesis increased (21). Taken together inhibiting the COX-2 activity apparently improves outcome in active TB. A highly significant publication concludes that a human intervention study with anti-inflammatory drugs to TB patients receiving standard chemotherapy should be designed based on their murine data demonstrating reduced *Mtb* load and lung lesions as well as better survival of animals treated with ibuprofen (22).

### 1.2.2 Clinical studies of COX-2i

In three clinical explorative trials, we have demonstrated that COX-2i improves the immune functions of HIV patients on ART (17-19). We have also showed for the first time that treatment with a COX-2i was able to downregulate chronic immune activation and improve T cell functions in asymptomatic HIV-infected patients who did not use antiretroviral therapy (19). In these patients, chronic immune activation was dampened as demonstrated; CD38 density on CD8+ T cells (primary endpoint) decreased by 24% by study week 12 and improvement of CD4+ T cell loss with 30 CD4 cells  $\mu\text{l}^{-1}\text{year}^{-1}$ . Celecoxib further reduced the inhibitory surface receptor programmed death 1 (PD-1) on CD8+ T cells, improved humoral memory recall responses to a T cell-dependent vaccine and IL-6 tended to decrease in the treatment arm. In conclusion, celecoxib downmodulated the immune activation related to clinical progression of chronic HIV infection and improved T cell-dependent functions *in vivo*. There was an acceptable safety profile with celecoxib doses as high as 400 mg bid and no SAEs reported in any of the studies. Rash was observed in HIV patients without ART after receiving high-dose celecoxib in contrast to what we found with identical doses in patients on ART. Thus, it was concluded that this was associated by high HIV-induced immune activation levels itself and may have represented other bioprocesses than conventional drug allergies (19).

### 1.2.3 Pre-clinical studies of the H56:IC31 TB vaccine in animal TB models

H56 is a fusion protein of three mycobacterial antigens (Ag85B, ESAT-6, Rv2660c). Both Ag85B and ESAT-6 induce TB specific T cell responses that protect animals from *Mtb* challenge (23), whereas Rv2660c is preferentially recognized by latently infected individuals (24). The therapeutic post-exposure vaccine H56, developed at SSI, promotes a T cell response in mouse models with a high proportion of polyfunctional CD4 T cells that confers protective immunity and more efficient containment of late-stage infection than its predecessor the H1 (Ag85B-ESAT6) and BCG vaccines (23). This is also the first vaccine that demonstrates efficacy when administered post-exposure. H56 has been tested pre-clinically formulated with a range of adjuvants, most notably IC31® comprised of an oligodeoxynucleotide ODN1a complexed to a leucine and lysine containing polypeptide (25). The vaccine candidate combining H56 and IC31®, termed H56:IC (AERAS-456), seems to be immunogenic and protective also in non-human primates (26). However, some vaccinated non-human primates still demonstrate lack of H56:IC31 vaccine recall responses and experienced disease progression implying that strategies to boost vaccine responses should be tested.

